### CHARACTERISTICS OF THE SUBJECT POPULATION (3-10)

#### 3. ACCRUAL

- A. What is the number of subjects that must complete the study and be evaluable in order to achieve the scientific objectives of the research?** [See Educational Guide – Biomedical Research \(PedsIRB\)](#)

40 NICU infants who are between 23 and 32 weeks gestational age must complete the study.

- B. What is the statistical or other justification for the number of subjects needed to complete the study?** [See Educational Guide – Biomedical Research \(PedsIRB\)](#)

Based on our previous study, NICU infants who received 400 IU/day of Vitamin D are expected to have a mean discharge serum 25(OH)D of 23.1 ng/ml (standard deviation=7.0). Conservatively, the 800 IU dose group is expected to have a mean discharge serum 25(OH)D of 30 ng/ml (SD=7.0) (SD estimated from our previous study data). Assuming a 0.05 level of significance, and a total drop-out rate of 10 percent; 40 NICU infants randomized to the two dose groups will provide 81 percent power to detect a difference between doses.

- C. What is the maximum number of subjects that will be consented at all sites under the oversight of the PedsIRB and what is the justification for this number?** [See Educational Guide – Biomedical Research \(PedsIRB\)](#)

A maximum of 40 infants who are between 23 and 32 weeks gestational age will be consented for the study.

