## 8. INCLUSION CRITERIA

What are the specific inclusion criteria? [See Educational Guide – Biomedical Research \(PedsIRB\)](#)

Infants who are receiving inpatient care in the Newborn Intensive Care Nursery will be considered for enrollment. Prospective subjects who are between 23 and 32 weeks gestational age will be identified on admission to the Nebraska Medical Center Newborn Intensive Care Nursery.

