## METHODS AND PROCEDURES (11-15)

### 11. METHODS AND PROCEDURES APPLIED TO HUMAN SUBJECTS

- A. Does this protocol require tests to be performed for the purpose of determining subject eligibility which would not be *routinely* conducted as part of standard clinical care of the prospective subject?

☒ No

☐ Yes. Describe the tests to determine subject eligibility. [See Educational Guide – Biomedical Research \(PedsIRB\)](#)

- B. Indicate the study design by checking the appropriate boxes.

[See Educational Guide – Biomedical Research \(PedsIRB\)](#)

☐ Phase I

☐ Phase I/II

☐ Phase II

☐ Phase II/III

☐ Phase III

☐ Phase IV

☐ Other:

☐ Case-Control

☐ Cohort

☐ Cross-sectional

☐ Randomized, parallel group

☐ Randomized, cross-over

☐ Placebo-Controlled

☐ Single Blind

☒ Double Blind

☐ Triple Blind

- C. Describe sequentially all procedures, interventions and evaluations to be applied to subjects, including follow-up. [See Educational Guide – Biomedical Research \(PedsIRB\)](#)

Step 1: Recruitment and Informed Consent

Parents of infants admitted to the NICU who meet eligibility criteria will be approached by study personnel, information about the study will be given, and informed consent will be obtained.

Step 2: Collection of Baseline Data

A sample of cord blood drawn that is drawn at birth for other routine clinical use will be frozen and stored at -70 degrees for study analysis of 25(OH)D levels. Demographic information will be obtained, including gestational age, birth weight, length, circumference, race, ethnicity, and season of birth. This is routine NICU admission information that is not performed exclusively for research purposes.

Step 3: Randomization

Study pharmacist will be notified and eligible infants will be randomized to the 400 IU/day of 800 IU/day supplementation group. Vitamin D supplementation will begin when the infant reaches full enteral feedings. Both the investigators and the subjects will be blinded as to the treatment group.

Step 4: NICU Data Collection

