Blood samples will be drawn every 4 weeks, beginning 4 weeks after birth. The maximum amount of blood taken at each blood draw will be 2 mL. The final blood draw will occur at 36 weeks CGA. Analysis of each blood sample will include 25(OH)D levels, PHT levels, and VDBP. A serum calcium will be obtained with each blood draw for safety monitoring purposes, if not already available from routine NICU lab monitoring. Lab draws in the NICU are done by the nursing staff and are done using heelstick or venipuncture, at the discretion of the nursing staff. Nurses may make more than one

attempt to draw blood, but if the lab draw cannot be successfully completed, the attempt is terminated at the discretion of the bedside nurse. Ongoing clinical data collection from the patients' medical record will include daily vitamin D intake, growth parameters, and infections/antibiotic use.

Step 5: Urine collection and DEXA Scan: When the infant reaches 36 weeks gestational age, a 24-hour urine sample will be obtained for measurement of calcium excretion. At 40-44 weeks gestational age, a DEXA scan will be performed.

| Test                                  | Frequency of Collection                                                                     | Amount of Blood                                                                                                                                                                                                                                                                    |
|---------------------------------------|---------------------------------------------------------------------------------------------|------------------------------------------------------------------------------------------------------------------------------------------------------------------------------------------------------------------------------------------------------------------------------------|
| 25(OH)D(ng/mL)                        | Collected on cord blood, every 4 weeks, and at 36 weeks CGA                                 | Requires < 0.5 mL                                                                                                                                                                                                                                                                  |

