The primary endpoint for statistical analysis is serum 25(OH)D level at discharge. Analysis will be done using intent-to-treat strategy, where infants will be included in the group to which they were assigned regardless of compliance. The statistical analyses will be done with SAS software. P-values less than 0.05 will be considered statistically significant. Baseline characteristics (e.g. gender, season of birth) will be compared between the dose groups, stratified by race and gestational age, to ensure comparability of the groups using Mann-Whitney tests for continuous variables and Fisher's exact tests for categorical variables. Analysis of covariance (ANCOVA) will be conducted to test for differences in discharge serum 25(OH)D level between the dose groups while adjusting for known confounders (race, gestational age, gender and season of birth). If the overall F-tests are significant then pairwise comparisons will be made and p-values for these comparisons will be adjusted for multiple comparisons using Tukey's method. Correlation methods will be used to look at associations between 25(OH)D levels and iPTH levels at discharge. Descriptive plots will be used to evaluate changes in serum 25(OH)D levels. DEXA scan results evaluating total body minus head bone mineral density (BMD) will be compared between the two groups. Descriptive plots will be used to evaluate changes in serum 25(OH)D levels. All tests will be 2-sided and p-values <0.05 will be considered statistically significant.

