**2) What is the frequency of data analysis?**

*See Educational Guide – Biomedical Research (PedsIRB).*

**E. Describe the specific subject withdrawal criteria. If *none*, provide an explanation. *See Educational Guide – Biomedical Research (PedsIRB)***

A subject will be withdrawn from the study at the request of the parent or attending neonatologist. A subject would be withdrawn from the study with the diagnosis of GI, liver, or kidney disease, inborn errors of metabolism, parathyroid disease, disorders of calcium metabolism, and any condition requiring treatment with seizure medication or steroids. A subject could also be withdrawn at the request of the parent or guardian. Ongoing monitoring of the data will allow for any subject with lab abnormalities related to vitamin D or calcium to be withdrawn from the study. A subject would be withdrawn with a serum calcium above 12.5 mg/dl after initiation of the vitamin D, or a 25(OH)D level above 150 ng/mL.

**F. Describe the specific stopping rules for the research. If *none*, provide an explanation. *See Educational Guide – Biomedical Research (PedsIRB).***

The study would be stopped in the event that even a small amount of the infants enrolled in the study (>5 infants) developed hypercalcemia (serum calcium above 12.5, ionized calcium about 1.35) or hypervitaminosis D (25(OH)D levels above 150 ng/mL).

**G. Describe the auditing plan for the research (i.e., who will conduct the audit and how often). If *none*, provide an explanation. *See Educational Guide – Biomedical Research (PedsIRB)***

None

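### Randomisation is not tied to the start of dosing, so allocations can go to infants who are never dosed before the last blood draw

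*Protocol*

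**What the plan says.** - **Identification and consent.** Under section 8, prospective subjects "will be identified on admission to the Nebraska Medical Center Newborn Intensive Care Nursery". Section 27 has screening at admission and a second approach to parents within 72 hours of first contact.
- **Order of procedures.** Section 11.C answers a request for a sequential description: Step 1 consent, Step 2 baseline data and cord blood, Step 3 randomisation through the study pharmacist. No day or trigger is given for randomisation. Neither sections 8 and 9 nor Step 3 makes feeding status a condition of it.
- **Start of dosing.** The same Step 3 says: "Vitamin D supplementation will begin when the infant reaches full enteral feedings". There is no latest date for this and no instruction to repeat the section 9 check when it happens.
- **Last sample.** Section 11.C Step 4: "The final blood draw will occur at 36 weeks CGA". Section 11.E calls the primary endpoint the discharge level, but no later study draw is scheduled.
- **Analysis.** Section 11.E is by intent to treat: "infants will be included in the group to which they were assigned regardless of compliance".
- **Withdrawal.** Section 18.E: "A subject would be withdrawn from the study with the diagnosis of GI, liver, or kidney disease". It extends this to the other listed medical conditions and to treatment with seizure medication or steroids. It does not say whether withdrawn infants are still sampled and analysed.
- **Sample size.** Section 3.B plans on infants who received the 400 IU dose, who "are expected to have a mean discharge serum 25(OH)D of 23.1 ng/ml (standard deviation=7.0"), against 30 ng/mL on 800 IU. It allows 10% dropout and makes no allowance for undosed infants. Section 3.C caps consent at 40, and section 26.D expects no withdrawals.

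**The concern.** The two arms can begin to differ only once supplementation starts. If allocation comes earlier, anything that keeps an infant from reaching that point happens after randomisation, and the infant still occupies one of 40 places.

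There are two routes, with different consequences. An infant who survives, stays in the study and is sampled at 36 weeks without ever being dosed has an expected level unrelated to its arm, so it pulls the intent-to-treat difference towards zero. An infant who dies, or is withdrawn under section 18.E, before the first dose will usually have no endpoint value and is a lost allocation.

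The planned difference describes infants who received the supplement, whereas the analysis covers everyone assigned. The trial is small and its power only just clears 80%, so there is little room for either route. An analysis plan written later cannot recover an allocation already spent.

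**Working it through.** **Inputs.** From section 3.B: means 23.1 and 30 ng/mL (difference 30 − 23.1 = 6.9), SD 7.0, 40 infants, 10% dropout, stated power 81%, "Assuming a 0.05 level of significance". From section 11.E: "All tests will be 2-sided and p-values <0.05 will be considered statistically significant". Equal allocation is assumed because no ratio is given. Evaluable infants: 40 × 0.9 = 36, or 18 per arm.

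**Formula.** Two-sample t-test, noncentrality λ = Δ / (SD × √(2/n)), with 2n − 2 degrees of freedom. Power is the probability that the noncentral t statistic exceeds the two-sided 5% critical value.

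**Step 1: the plan's own figure.** λ = 6.9 / (7 × √(2/18)) = 6.9 / 2.333 = 2.96 on 34 degrees of freedom. Power is 81.9%, which matches the stated 81% to within a point. It requires all 36 analysed infants to carry the full 6.9 ng/mL difference.

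**Step 2: undosed but analysed.** If a share f of the analysed infants in each arm has had no dose, Δ = 6.9 × (1 − f). With 18 per arm and SD 7:

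| Assumed f | Δ (ng/mL) | Power | Total N for 81% power with 10% dropout |
|---|---|---|---|
| 0% | 6.90 | 81.9% | 40 |
| 5% | 6.55 | 77.9% | 45 |
| 10% | 6.21 | 73.4% | 49 |
| 20% | 5.52 | 63.3% | 60 |

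The last column is 2n/0.9 rounded up, with n = 18, 20, 22 and 27 per arm. The consent cap is 40.

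**Step 3: sensitivity to the SD.** Undosed infants may also widen the spread. Suppose they sit at 17.6 ng/mL, the cord-blood mean of the previous study (infants above 32 weeks, so a further assumption here). Each arm's variance is then 49 + f(1 − f)(arm mean − 17.6)². At f = 10% this is 49 + 0.09 × 5.5² = 51.7 and 49 + 0.09 × 12.4² = 62.8. The average is 57.3, giving SD 7.57 and power 66.7%. At f = 20% the SD is 7.98 and power 52.2%.

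**Step 4: lost instead of analysed.** If pre-dose events remove infants, Δ stays at 6.9 and n falls. Counting all losses from 40, including the planned 4:

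| Total lost | n per arm | Power |
|---|---|---|
| 4 | 18 | 81.9% |
| 6 | 17 | 79.6% |
| 8 | 16 | 77.0% |
| 10 | 15 | 74.1% |

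**Step 5: longest possible exposure.** From birth to the last draw there are 36 − 23 = 13 weeks for an infant born at 23 weeks, and 36 − 32 = 4 weeks for one born at 32 weeks. Time to full feeds comes off both.

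**The case against.** The strongest reply is that the protocol never says infants are randomised early. A reader might infer it from admission screening, the 72-hour consent window and the step order, but only screening and consent carry a time. Step 3 puts pharmacist notification, allocation and the start of supplementation in one paragraph, and that also fits a pharmacist being called when an infant is ready to start. This stands: early allocation is permitted, not prescribed.

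A reader might also infer that every infant who becomes ineligible before dosing dilutes the comparison. The text does not support that. Section 18.E withdraws most such infants, and an infant who dies has no serum level at 36 weeks. These are mainly losses, which the 10% dropout allowance partly covers, and they cost less than dilution does. Sections 11.E and 18.E still need reconciling on whether withdrawn infants are followed and analysed.

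It is also fair to say that no document figure gives the undosed share, and that counting a barely dosed infant as having no effect would overstate dilution. The planning values come from the previous study's discharge levels and may already reflect limited inpatient exposure, so the 4-week ceiling does not by itself show that 6.9 ng/mL is too large.

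Finally, how undosed infants enter the analysis set could be left to the analysis plan. When allocation occurs, and what is checked at that moment, belongs in the protocol.

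**Conclusion.** The point holds as a gap in the design: the interval between randomisation and first dose is uncontrolled, and the sample size has no allowance for it. The consequence is lost power. Pre-dose events under blinding should fall equally on both arms, so type I error is not inflated, and intent to treat is the right principle.

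On the protocol's own inputs, 81.9% power falls to 77.9% at 5% undosed, 73.4% at 10% and 63.3% at 20%. If the infants are lost instead, it falls to 77.0% with 8 lost and 74.1% with 10 lost. All these shares are assumed, so the tables show how thin the margin is and do not forecast the trial's power. Even the 5% case goes below 80%.

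This should be changed because the remedy is cheap. Confidence is high that the text leaves the interval open, and only moderate that early allocation would happen in practice.

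**What to change.** - Keep consent and cord-blood storage at admission.
- State in section 11.C Step 3 that the pharmacist randomises on the day the infant meets the protocol's existing condition for starting supplementation, and only if that day comes before the 36-week draw.
- Re-check the section 9 exclusions that day. Infants lost earlier count as consented but not randomised.
- Restate the section 3.C cap of 40 as infants randomised. That form item asks for a consent maximum, so a higher one can be given beside it.
- State whether infants withdrawn under section 18.E are still sampled and analysed, so that it agrees with section 11.E.

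With f = 0, 40 infants remain enough (81.9%).

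**Cost.** A few more families consent whose infants are never randomised, and the result applies to infants who reach full feeds. Because study draws begin 4 weeks after birth, the protocol must also say whether that draw is taken in consented infants not yet randomised.

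**What it does not cure.** Infants born near 32 weeks, or reaching full feeds shortly before 36 weeks, would still have short exposure. The protocol should acknowledge this. No change to the dose or the feeding rule is implied.

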| Serum Calcium (For safety monitoring) | Collected with each 25(OH)D draw                                                            | Will be collected for study purposes only when not drawn as part of routine NICU labs (requires 0.5 mL)                                                                                                                                                                            |
| PTH                            | Collected with each 25(OH)D draw                                                            | 1 mL                                                                                                                                                                                                                                                                               |
| VDBP                           | Collected with each 25(OH)D draw                                                            | 0.1 mL (included in the 0.5 for 25(OH)D)                                                                                                                                                                                                                                           |
| TOTAL                          | Max blood draws on any 1 infant, not including cord blood: Every 4 weeks from 24-36weeks: 3 | 2 mL maximum every 4 weeks A volume of 4 mL in 8 weeks will allow an infant with a weight of 1300 grams to remain within the guidelines of 3 mL/kg of blood for study purposes in an 8 week period. Protocol adjustments will be made to minimize blood volumes in smaller infants |

**D. Identify any procedures, interventions, and evaluations that are experimental or performed exclusively for research purposes. *See Educational Guide – Biomedical Research (PedsIRB)***

Procedures performed exclusively for research purposes include:

1. Acquisition and storage of cord blood for analysis.
2. Blood samples taken every 4 weeks for analysis of 25(OH)D, iPTH, serum calcium, and VDBP.
3. 24 hour urine collection for calcium excretion
4. DEXA scan after discharge at term corrected age

24-hour urine collection for 24 hour calcium excretion will be collected using an infant urine collection bag that is placed in the infants' diapers. The bags are attached to the skin as per the manufacturer's instructions and are changed with every diaper change to minimize any risk of skin breakdown.

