A serum calcium levels will be run on the blood sample for study purposes only if the infant does not have a serum calcium level available at the time point (within 72 hours) of the study draw. NICU hospitalized infants have routine clinical monitoring of laboratory values and this routinely includes serum calcium levels. If a serum calcium level is available, it will be used as the value for study purposes, and will decrease the amount of blood required for study purposes.

Guidelines used for blood draw limits for this study was 3 mL/kg over an 8 week period. This volume would allow an infant with a birth weight of 1.3 kg to complete our protocol as written. If the birth weight of the infant is less than 1.3 grams, the volume allowed for the study over the next 8 weeks will be calculated and protocol adjustments will be made. Examples of protocol modifications will be: use of clinically available serum calcium, if not available, ionized calcium could be used for safety monitoring purposes with less than 0.3 mL of blood. The investigators

could also eliminate the VDBP assay in this infant (as this is an exploratory aim) to reduce the amount of blood needed. 25(OH)D on the volume of blood remaining after a CBC is run, this option could be investigated to reduce blood draw volume.

**E. Describe briefly the statistical methods used to analyze the data.** [See Educational Guide – Biomedical Research \(PedsIRB\)](#)

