**RISK/BENEFIT ASSESSMENT (16-22)**

**16. POTENTIAL RISKS**

**What are the potential risks associated with each research intervention? If data are available, estimate the probability that a given harm may occur. See Educational Guide – Biomedical Research (PedsIRB)**

This study will be presented as a greater than minimal risk for physical and psychological harm.

Supplemental vitamin D3 400 IU or 800 IU will be given to the respective groups. Hypercalcemia has been associated with supplementation resulting in serum levels of above 150 ng/mL. Based on preliminary data, we do not expect our supplementation protocol to achieve 25(OH)D levels of >30 ng/mL. We would not expect this dose of vitamin D to carry any potential risk to the subject, in fact this dosing is consistent with an American Academy of Pediatrics guideline that recommends all term, healthy infants consuming less than 1000 mL of formula a day receive 400 IU vitamin D3 supplementation, and the European Society for Gastroenterology, Hepatology, and Nutrition recommendation that premature infants receive 1000 IU/day of vitamin D3 (18).

Hypersensitivity to vitamin D resulting in hypercalcemia can occur in individuals with primary hyperparathyroidism. Infants with this condition would be excluded from the study.

Study subjects would also have increased blood draws for study purposes compared to infants not enrolled in the study. Each subject would have approximately 4 mL of blood drawn over the course of 8 weeks (2 mL per 4 weeks) that a non-study infant would not be exposed to. Increased phlebotomy can result in anemia and risk of infection. Many blood draws are for routine care in the Intensive Care Nursery, so blood for study purposes would be drawn at the same time as patient care labs whenever possible to avoid a painful procedure for the infant. Collection of a urine sample represents minimal risk to an infant, there is a small risk of skin breakdown which is minimized by changing the collection bag every 24 hours.

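### The research blood-volume figures do not follow from the sampling schedule: infants born before 28 weeks have three draws within 8 weeks, up to 6 mL (4.5 mL with routine calcium) against the stated 4 mL

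*Protocol*

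**What the plan says.** Section 8 admits infants by gestational age: "Prospective subjects who are between 23 and 32 weeks gestational age". Step 4 of section 11.C sets the schedule: "Blood samples will be drawn every 4 weeks, beginning 4 weeks after birth", and then "The final blood draw will occur at 36 weeks CGA". Each draw may take up to 2 mL. The table lists the 36-week sample alongside the 4-weekly ones: "Collected on cord blood, every 4 weeks, and at 36 weeks CGA".

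The TOTAL row of that table gives "Max blood draws on any 1 infant, not including cord blood: Every 4 weeks from 24-36weeks: 3", a ceiling of 2 mL per 4 weeks, and "A volume of 4 mL in 8 weeks will allow an infant with a weight of 1300 grams to remain within the guidelines", the guideline being 3 mL/kg in an 8-week period. Section 11.D draws the consequence: "This volume would allow an infant with a birth weight of 1.3 kg to complete our protocol as written". Below that birth weight the allowed volume is worked out for the infant and the protocol is adjusted. The trigger for this is printed as 1.3 grams.

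Section 16 gives the IRB the same volume: "Each subject would have approximately 4 mL of blood drawn over the course of 8 weeks (2 mL per 4 weeks".

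**The concern.** The 4 mL figure treats the schedule as a rate, 2 mL per 4 weeks over 8 weeks. The schedule is a list of dates. Three draws 4 weeks apart span only 8 weeks, and the fixed 36-week draw usually falls less than 4 weeks after the one before it. The draw count, the 8-week volume and the weight threshold may therefore all be too low for the infants with the most draws.

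Section 16 names anemia and infection as harms of added phlebotomy and classes the study as greater than minimal risk. The 4 mL and 1.3 kg figures are what the IRB has for judging that burden, and 1.3 kg decides which infants get an adjusted protocol.

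**Working it through.** **Inputs.** Birth at 23 to 32 weeks (section 8). First draw at birth + 4 weeks, then every 4 weeks, with the last at 36 weeks CGA (11.C, Step 4). Volumes from the 11.C table: under 0.5 mL for 25(OH)D, which includes VDBP; 1 mL for PTH; 0.5 mL for calcium, taken only when no routine value is available. Limit: 3 mL/kg per 8 weeks (11.D).

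**Volume per draw.** 0.5 + 1 + 0.5 = 2 mL, the stated maximum. With routine calcium: 0.5 + 1 = 1.5 mL.

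**The plan's own figures.** Minimum weight = 8-week volume / 3 mL/kg = 4 / 3 = 1.33 kg, which the plan rounds to 1.3 kg (4 / 1.3 = 3.08 mL/kg). That rounding is not the issue. The maximum of 3 draws matches birth at exactly 24 weeks: 28, 32 and 36 weeks.

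**Draws by gestational age at birth** (birth + 4, + 8, + 12 weeks while before 36 weeks, plus 36 weeks):

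| Birth (weeks) | Draws (weeks CGA) | Total draws | Most draws in any 8 weeks | Max mL in 8 weeks |
|---|---|---|---|---|
| 23 | 27, 31, 35, 36 | 4 | 3 | 6 |
| 24 | 28, 32, 36 | 3 | 3 | 6 |
| 25 | 29, 33, 36 | 3 | 3 | 6 |
| 26 | 30, 34, 36 | 3 | 3 | 6 |
| 27 | 31, 35, 36 | 3 | 3 | 6 |
| 28 | 32, 36 | 2 | 2 | 4 |
| 29 | 33, 36 | 2 | 2 | 4 |
| 30 | 34, 36 | 2 | 2 | 4 |
| 31 | 35, 36 | 2 | 2 | 4 |
| 32 | 36 | 1 | 1 | 2 |

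Counted by day, 34 of the 35 birth ages from 23w0d to 27w6d have three draws in strictly less than 8 weeks. The exception is 24w0d, where the three span exactly 8 weeks. The four draws of a 23w0d infant run from 27 to 36 weeks, which is 9 weeks. Its total is up to 8 mL, but its 8-week maximum is 6 mL.

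**Consequence at 3 mL/kg.**

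| Three draws | mL in 8 weeks | Above 4 mL by | Weight needed | mL/kg at 1.3 kg |
|---|---|---|---|---|
| Full draws | 3 × 2 = 6 | 50% | 6 / 3 = 2.0 kg | 6 / 1.3 = 4.6 (54% over) |
| Routine calcium throughout | 3 × 1.5 = 4.5 | 12.5% | 4.5 / 3 = 1.5 kg | 4.5 / 1.3 = 3.5 (15% over) |

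For three draws to fit at 1.3 kg, each could average at most 3 × 1.3 / 3 = 1.3 mL, and PTH alone takes 1 mL of that.

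**The case against.** The best defence is that the protocol's wording can yield 4 mL. There are two routes.

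- **Count the 8 weeks from birth.** Section 11.D works out a small infant's allowance for the 8 weeks that follow. On that count, births at 23 to 31 weeks have two draws, so 4 mL. But the guideline is worded as any 8-week period, and this count leaves out a third draw that falls within 8 weeks of the first (born at 25 weeks: 29, 33, 36).
- **Read 2 mL per 4 weeks as a binding cap.** The cap then conflicts with the schedule, because two draws of up to 2 mL can fall 1 to 3 weeks apart. Birth at 27 weeks gives draws at 35 and 36 weeks. Births at 29 to 31 weeks meet the same conflict, although their 8-week total stays at 4 mL.

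Both routes show that the wording is ambiguous. Neither makes the passages agree.

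Three parts of the defence stand. First, 2 mL is a maximum, and the protocol says NICU monitoring routinely includes calcium, so 4.5 mL may be closer to practice than 6 mL. Second, infants below 1.3 kg get an individual calculation. Third, nursing staff may end an unsuccessful attempt, so not every scheduled draw will be obtained.

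A reader might infer that the least mature infants in general will be sampled beyond 3 mL/kg, or that a small infant's individual allowance would be shared over two draws and then exceeded by a third. The documents support neither. Infants below 1.3 kg are to be adjusted to the limit, and nothing says how the allowance is divided among draws.

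**Conclusion.** The inconsistency is real. For births before 28 weeks the schedule gives three draws in 8 weeks: up to 6 mL, or up to 4.5 mL with routine calcium, against the 4 mL in the 11.C table and section 16. At 23 weeks it gives four draws against a stated maximum of 3. The weight at which three draws fit the protocol's own limit is 2.0 kg (1.5 kg with routine calcium), so the statement that a 1.3 kg infant can complete the protocol unmodified does not hold for these births.

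Infants who could pass the limit without triggering an adjustment are those born before 28 weeks who weigh 1.3 to under 2.0 kg, or 1.3 to under 1.5 kg with routine calcium. The protocol gives no weight distribution, so the number is unknown and may be small.

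The result assumes that the 4-weekly draws and the 36-week draw are both taken as scheduled, that the 8-week window may start at any draw, that each draw is at the listed volume, and that weight is birth weight, as in 11.D, with no allowance for later growth. For births at 28 weeks or later the 4 mL figure holds. The point concerns the stated sampling burden and does not touch the primary comparison.

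**What to change.** Reconcile four places: the schedule in 11.C Step 4, the TOTAL row of the 11.C table, the 11.D text on blood limits, and section 16. The maximum number of draws, the 8-week volume and the weight threshold should all follow from one schedule. State whether the 8 weeks run from birth or cover any 8-week period, and whether 2 mL per 4 weeks is a cap or a description. Correct the trigger weight in 11.D from grams to kilograms, to agree with the 1.3 kg and 1300 grams given elsewhere. Whether the schedule or the stated figures change is for the sponsor and the IRB.

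The cost is an amendment of wording. If the schedule stays, the volume shown to the IRB becomes less favourable and more infants may need the adjustment that the protocol already foresees. If the schedule changes, some infants have fewer or differently timed samples.
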